### Sample size

A convenience sample of 50 patients and 50 informal caregivers per phase (25 CHF and 25 COPD patients and their informal caregivers for the baseline phase and 25 CHF and 25 COPD patients and their informal caregivers for the intervention phase) has been set as a target based on the following rationale. We use as a reference a two-sample *t* test on the total POS scores, assuming a minimally relevant difference of 4, i.e., 10% of the best score 40, and a common standard deviation of 6, which constitutes the worst case based on previous studies [33, 34]. In order to obtain 80% power at a significance level of 5%, a total of 37 patients per group will be required. To this number, we will add a 30% attrition rate which results in 50 patients and caregivers per group. We will retrospectively compute our standard deviation with an interim analysis once three fourths of the originally planned sample size has been collected to examine whether upward revisions are required.

It is important to note that due to the shortage of studies similar to ours, attrition rates for the population of interest are not well understood. As a starting point, we have used attrition rates from integrated palliative care cancer studies and we aim to retrospectively evaluate the suitability of these rates.

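### The interim look can revise the sample size on the standard deviation alone; no revision is tied to attrition, and 50 per group gives 78.5% power, not 80%, at the plan's own 30% loss

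*Protocol article*

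**What the plan says.** All of this is in the Sample size section of the protocol article.

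- Test: "We use as a reference a two-sample *t* test on the total POS scores".
- Difference that the calculation is meant to detect: "assuming a minimally relevant difference of 4, i.e., 10% of the best score 40".
- Spread: "a common standard deviation of 6, which constitutes the worst case based on previous studies".
- Result: "In order to obtain 80% power at a significance level of 5%, a total of 37 patients per group will be required". A 30% attrition allowance then brings this to 50 per group.
- Interim look: "We will retrospectively compute our standard deviation with an interim analysis once three fourths of the originally planned sample size has been collected". Its stated purpose is to see whether the size must go up.
- Attrition: the next paragraph says that "attrition rates for the population of interest are not well understood", that rates from cancer studies served as a starting point, and that "we aim to retrospectively evaluate the suitability of these rates".

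No section links observed attrition to a change in sample size. Table 3 under Feasibility assessment has a retention item, but it is a question to be answered in the report and triggers nothing.

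**The concern.** Two uncertain inputs produce the 50 per group: the SD and the attrition. The plan regards its SD as pessimistic and says openly that it does not know the attrition. Yet the only rule that can enlarge the study looks at the SD. If losses in this population exceed those in the cancer studies, the number of 3-month scores falls, power falls with it, and the look can still report that nothing needs revising.

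The design gives some reason to expect loss. Patients have advanced disease with a readmission, the surprise question excludes those whose death within a year would be unexpected, and most follow-up questionnaires go by post. The stake is the power claim attached to the aim, stated in the Aim section, of testing whether early integration improves quality of life and quality of care.

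**Working it through.** **Inputs from the Sample size section:** difference 4, SD 6, significance level 5%, power 80%, 50 enrolled per group, attrition 30%. Sidedness is not stated. Two-sided is assumed, because it reproduces the plan's figure and one-sided does not (28 per group by the normal approximation).

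**Step 1: reproduce the plan.** Standardised difference = 4/6 = 0.667. The two-sample t test (noncentral t) needs n = 36.3, so 37 per group, as stated. Power at 37 per group is 80.8%.

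**Step 2: the attrition allowance.** Enrolment that leaves 37 after 30% loss is 37/(1 − 0.30) = 52.9, so 53. Multiplying instead gives 37 × 1.30 = 48.1, so the stated 50 sits nearer to the multiplying form. Read backwards, 50 per group tolerates a loss of 1 − 37/50 = 26%.

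**Step 3: power with 50 enrolled per group.** Completers = 50 × (1 − loss); difference 4, SD 6. Only the 30% row is the plan's own rate; the others are assumed, because the documents give no figure for heart failure or chronic obstructive pulmonary disease.

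| Loss | Completers per group | Power |
|---|---|---|
| 20% | 40 | 83.8% |
| 26% | 37 | 80.8% |
| 30% (plan) | 35 | 78.5% |
| 40% | 30 | 71.9% |
| 50% | 25 | 63.7% |

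In every row the SD equals the planned 6, so a check on SD alone gives no reason to revise.

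**Step 4: how far a smaller SD would compensate.** The largest SD that still gives 80% power is 5.9 at 30% loss, 5.4 at 40% and 4.9 at 50%. With SD 5, power is 86% at 40% loss and 79% at 50%. With SD 5.5 it is 79% at 40% loss.

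**Step 5: what a revision can achieve when the phases are sequential.** If three fourths means 75 of the 100 patients, the 50 baseline patients are all in and only the intervention group can grow. Take 40% loss, so baseline is fixed at 50 × 0.60 = 30 completers:

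- Dividing 37 by (1 − 0.40) gives 61.7, so 62 intervention patients and about 37 completers. Power for 30 versus 37 is 76%.
- Reaching 80% against 30 baseline completers takes about 46 intervention completers, or 46/0.60 = 76.7, so 77 enrolled.

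The usual inflation formula therefore falls short once baseline recruitment has closed.

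**The case against.** The strongest reply is that this is a feasibility study with a convenience sample, in which the t test is only a reference and learning the attrition is one of the outputs. The 30% is disclosed as provisional, telephone reminders and completion at check-ups limit loss, and an expected survival of at least 6 months is required against a 3-month follow-up. Re-estimating on the SD alone is a recognised choice. It is also useful here, since the SD could exceed 6 (SD 7 with 35 per group gives 65%). All of that stands, and it limits the weight of the point. It does not remove the point, because the section still claims 80% power and its own 30% loss does not deliver it.

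Three stronger readings are tempting and are not supported:

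- *The look would never be reached.* Three fourths of 100 is 75, while 30% loss leaves only 70 completed 3-month forms. This holds only if the count is of 3-month forms against the enrolment target. The more natural reading counts patients recruited, which attrition cannot block. Against the 74 evaluable patients, three fourths is 55.5, which is below 70.
- *Attrition will be judged only after the study ends.* The plan uses the same adverb, retrospectively, for the interim SD calculation, so the attrition review could also happen mid-study. What the text does show is that no revision is attached to it.
- *Power will fall well below 80%.* That needs an SD near 6 together with a loss of around 40% or more, and the documents support no such loss figure. If the SD is as conservative as the plan says, it cushions the loss, as Step 4 shows.

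**Conclusion.** The concern holds in a limited form. The revision rule covers the input that the plan calls a worst case and omits the one it calls poorly understood. At the plan's own inputs the shortfall is small: 78.5% against 80%, because 50 per group absorbs only 26% loss. On the assumed range it grows to 72% at 40% loss and 64% at 50%, and a look at the SD alone would not show it unless the SD also exceeded 6. These figures assume a two-sided test, equal loss in both groups, and an SD of exactly 6; a lower SD would offset part or all of the loss. The point merits a change to the stated rule and the stated power. It does not invalidate a feasibility study.

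**What to change.** In the Sample size section:

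1. At the existing look, compute the share of patients due at 3 months who returned a usable POS, alongside the SD. Base any revision on both together.
2. Say what three fourths counts: patients enrolled, or patients who have reached 3 months.
3. Compute any revision for unequal groups with the baseline completers fixed, as in Step 5. Alternatively, make the attrition check before baseline recruitment closes. With the planned 8-month phase, patients included in the first 8 − 3 = 5 months will have reached follow-up by then.
4. Whether or not the size is revised, replace the single 80% by power over a stated attrition range, for example 20% to 50%, including 78.5% at 30%.

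The cost is a few sentences, one count from forms that are collected anyway, and a less favourable stated power. More patients follow only if the sponsor uses the upward revision that the plan already allows.

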### Duration and setting

The overall study is estimated to last 24 months and will be conducted in UZ Leuven in the Departments of Cardiology and Pulmonology (two nursing wards for CHF and one for COPD). We estimate 8 months duration for the baseline and the intervention phase and 3 months for the training period. An overall time delay of 25% has also been added to the timeline.

### Feasibility assessment

For the feasibility assessment of our study, we have employed the analytical framework of Bugge et al., adapted directly from Kane et al. [35, 36]. The assessment is reported in Table 3 where the researchers have to complete the findings and evidence columns for each of the 14 methodological issues.

**Table 3 Tab3:** Feasibility assessment of 14 methodological issues

Methodological issues	Findings	Evidence
1. Did the feasibility study allow a sample size calculation for the main trial?		
2. What factors influenced eligibility and what proportion of those approached were eligible?		
3. Was recruitment successful?		
4. Did eligible participants consent?		
5. Were participants successfully randomized and did randomization yield equality in groups?		
6. Were blinding procedures adequate?		
7. Did participants adhere to the intervention?		
8. Was the intervention acceptable to the participants?		
9. Was it possible to calculate intervention costs and duration?		
10. Were outcome assessments completed?		
11. Were outcomes measured those that were the most appropriate outcomes?		
12. Was retention to the study good?		
13. Were the logistics of running a multicenter trial assessed?		
14. Did all components of the protocol work together?		

### Questionnaires

The CANHELP Lite Questionnaire is a tool that is often used in clinical PC studies to evaluate the quality of care [28]. This is a validated questionnaire with two versions: one version for patients and one for the informal caregivers. It can be used in both inpatient and outpatient care settings, and it has a completion time of approximately 10 min. The patient version has 21 questions that address the satisfaction of the quality of care, relationship with the doctors, illness management, communication, decision-making, and a question concerning the patient’s inner peace. For the caregivers, the questionnaire includes 23 questions assessing the satisfaction of the overall care, the relationship with the doctors, the characteristics of doctors and nurses, the illness management, the communication, the decision-making, and the involvement of the informal caregiver to patient’s care.

The POS is a validated tool that is frequently used in PC studies to measure (i) the quality of life and (ii) the symptoms of patients. This questionnaire has two versions, one for patients and one for informal caregivers, and it has a completion time of approximately 7 min [29]. This questionnaire consists of 12 questions, same for both patients and informal caregivers addressing their overall quality of life including physical and emotional symptom management and adequacy of information received.

The Advance Care Planning Questionnaire was developed by the Palliative Support Team of UZ Leuven, and it is used to measure different elements of advance care planning. It has three versions: one for patients, one for the informal caregivers, and one for healthcare providers (in this study, the patient and informal caregiver versions will be used). It has a completion time of approximately 10 min. Due to the fact that currently there exist no questionnaires that measure existing advance care planning aspects, this questionnaire is considered the most suitable for the goal of our study; however, it is yet to be validated. This questionnaire addresses questions over the perceptions of patients and caregivers concerning the current care, usefulness of discussions related to patient’s health, desire for involvement in these discussions in the present and the future, and evaluation of their emotional condition.

### Recruitment

According to the design of the study, and following discussions with the healthcare providers of pulmonology and cardiology wards, the following model for the identification of eligible patients will be adopted. The researcher, in charge after screening the patients’ electronic hospital files and after consulting with the head nurses of the cardiology wards and participating in their weekly multidisciplinary meetings of the wards, will identify the eligible CHF patients. For COPD, a pulmonology ward nurse is appointed to screen and report the eligible patients to the researcher upon examining the electronic files of the patients and cross-checking with assistant physicians of the corresponding ward during bilateral or multidisciplinary meetings. The information of the eligible COPD patients will be communicated via e-mail with the researcher. If any difficulties occur in the implementation of the recruitment process, the research team will perform the necessary adjustments so as to enhance the recruitment process.

### Data collection

The main researcher (NS) will explain the study protocol to both patient that meets the inclusion criteria and his/her most important informal caregiver. The patient will receive the informed consent document. After 1 or 2 days of reflection time, the main researcher will contact them again personally to ask if they like to join the study. If the patient and informal caregiver decide to participate in the study, they will provide their signed consent.

After the completion of the informed consent, the participants (patients and their informal caregiver) will be requested to fill in the three questionnaires in two timings: (1) at inclusion moment after signing the informed consent during the hospitalization of the patient and (2) at a follow-up of 3 months after inclusion (for both control and intervention groups). If a patient or an informal caregiver has difficulty understanding the questionnaires, the researcher in charge can provide additional information and help the participants fill in the questionnaires. When the eligible patients or their informal caregivers decline to participate, the researcher will ask for the reason and archive it. No special document will be provided to patients who will decline. Communication of the reason for not participating will be collected by the recruiter based on oral communication and without a predefined set of options in order to capture a broader spectrum of answers.

For the second measurement after 3 months, the same questionnaires will be sent by post to each patient and their caregiver and will be sent back to the researcher after they are completed. In some cases, the follow-up questionnaires will be administered to the patients when they visit the hospital for a checkup examination. When the follow-up questionnaires that have been posted are not returned back on time, the researchers will then contact the participants by telephone to remind them to complete and post the questionnaires back. The same process will be repeated for each patient and his/her caregiver for the intervention phase and after the implementation of the intervention. The study procedure for patients and their informal caregivers is described in Fig. 2.

**Fig. 2 Fig2:**
[figure not shown]
Study procedure for patients and their informal caregivers

### The intervention

After the completion of the baseline phase of the study (patients receiving standard care), the appointed intervention team for each ward will receive a training on how to apply the intervention in a 3-month period. The psychologist of UZ Leuven’s Palliative Support Care Team will be the one to train the personnel on how to apply the intervention to the experimental group. In cardiology, the assistant physicians will provide an introductory flyer for the intervention to the patient, and after the completion of this flyer, two psychologists and one psychology trainee will proceed with the implementation of the intervention. The same process will follow for the pulmonary ward, where after the introductory flyer by the assistant physicians, a specialist nurse, two ward nurses, and a spiritual counselor will proceed with the intervention.

The intervention will be based on the implementation of the early integrated palliative care planning intervention “My Wishes” (“MIJN WENSEN voor mijn Gezondheidszorg”), a content-validated communication tool for advance care planning in chronic disease developed by the Palliative Support Team in UZ Leuven (reference number 700864).

This tool addresses the wishes and needs of the patients concerning the delivery of care. It considers how the patient’s needs may be translated into treatment agreements for the present and the future taking into account the medical possibilities and limitations. MIJN WENSEN will be used as an invitation to communication and as a guide for conversations with the caregivers and for matching the current and future care with the treatment specialists. MIJN WENSEN can be also used as an informal declaration of intent, to register the patient’s indicated representative who will advocate the wishes of the patient in case she/he ever becomes unable of taking any decisions on their medical care. It can even be used as a formal declaration of intent, not only for the indication of a representative, but also the content of the treatment wishes for every type of mental incompetence.

Overall, MIJN WENSEN covers several components of the integrated PC like advance care planning, discussions on prognosis and illness limitations, provision of a holistic approach (physical, psychosocial, spiritual), patients’ goal assessment and continuous goal adjustment, financial issue discussions, DNR codes, (un)desirable treatments for current and future care, patients’ wishes, possibility of involvement of a PC team, and care for the last hours of life. Some components like the bereavement care and the early and direct involvement of a PC team are not included.

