**Fig. 1 Fig1:**
[figure not shown]
Sequence of the feasibility before-after intervention study

In both groups (control and intervention), patients and their most important informal caregiver will be asked to complete the Canadian Health Care Evaluation Project (CANHELP Lite) Questionnaire [28], the Palliative Outcome Scale (POS) Questionnaire [29], and the Advance Care Planning Questionnaire developed by the Palliative Support Team (at the University Hospital Leuven) to measure the current level of integrated PC in the following two timings: (i) inclusion moment after signing the informed consent and (ii) 3 months after inclusion (for both baseline and intervention groups). The methodology of this study was developed based on the SPIRIT guidelines.

We decided to jointly study CHF and COPD due to the fact that these two chronic, high prevalence, and non-malignant diseases share heavy physical and psychosocial symptom burden and similarly complicated disease trajectories, and currently, they are not curable [30, 31]. Moreover, there is also empirical evidence that CHF/COPD specialists share similar views on the role of integrated PC for these two diseases [32].

Currently in our hospital, the acute wards outside oncology have access to the Palliative Support Team, but they typically call for it only in the last hours (in the best case, in the last 2–3 days) of a patient’s life. The personnel of the cardiology and pulmonology wards have no training on the provision of PC.

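### Delivery team is fully aliased with disease, while the only before-after comparison with a stated power combines both; the estimate should be stratified by disease and results shown by disease-and-team group

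*Protocol article*

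**What the plan says.** **Delivery.** The section The intervention gives both departments the same tool, the same trainer and the same opening step (a flyer from the assistant physicians). The staff who then hold the conversations differ. In cardiology "two psychologists and one psychology trainee will proceed with the implementation of the intervention"; in pulmonology "a specialist nurse, two ward nurses, and a spiritual counselor will proceed with the intervention". Training goes to separate teams: "the appointed intervention team for each ward will receive a training on how to apply the intervention in a 3-month period". Under Duration and setting, the sites are "two nursing wards for CHF and one for COPD".

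**Identification.** Under Recruitment, the researcher screens for CHF patients and a ward nurse screens for COPD patients. Under Data collection and Informed consent, the same main researcher explains the study and follows up about joining for everyone.

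**Sizing.** The Sample size section refers to a two-sample t test on total POS, "assuming a minimally relevant difference of 4, i.e., 10% of the best score 40". For the spread of scores it takes "a common standard deviation of 6, which constitutes the worst case based on previous studies". It arrives at 37 per group, raised to 50. Each phase is split by disease, for example "25 CHF and 25 COPD patients and their informal caregivers for the intervention phase".

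**Analysis.** Data analysis plans t tests on total scores between various pairs of groups. Its one example is within COPD, patients against caregivers. It does not say whether the before-after comparison is combined or by disease.

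**Rationale and limitations.** Under Methodology and study design: "We decided to jointly study CHF and COPD due to the fact that these two chronic, high prevalence, and non-malignant diseases share heavy physical". That passage goes on to psychosocial burden, trajectories, incurability and specialists' views. Limitations names the non-randomised design and the unvalidated questionnaire. Overlapping personnel appear there only as the reason against an RCT.

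**The concern.** The tool is described as a guide for conversations, so the person who holds the conversation is part of what is delivered. Every CHF patient in the intervention phase meets psychology staff, and every COPD patient meets nurses and a spiritual counselor. The reasons given for studying the diseases together concern the diseases and specialists' views of palliative care for them. They do not cover two delivery models.

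Two things are at stake. First, if the effect, adherence or acceptability differs between CHF and COPD, the study cannot say whether disease or team is responsible. The Aim section includes identifying barriers to administering the intervention, and Post-feasibility study planning foresees practical guidelines for both diseases and possibly a multi-hospital RCT, so who delivers is a design question for the next step. Second, an overall figure that ignores disease averages the two models. An unstratified t test is also exposed to any change in disease mix between the phases.

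**Working it through.** **Inputs.** Difference 4, SD 6, 80% power, 5% level, 30% attrition, and 25 CHF plus 25 COPD per phase (Sample size). Sidedness is not stated; two-sided is used because it reproduces the plan's figure. An even split of completers between diseases is an assumption.

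**1. The plan's own figure.** A two-sample t test with standardised difference 4/6 = 0.667 needs 36.3 per group by the noncentral t, so 37. This reproduces. Power with 37 per group is 80.8%.

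**2. Completers.** 50 × (1 − 0.30) = 35 per phase, or 17 to 18 per disease per phase. Power for 4 points with 35 per phase is 78.5%.

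**3. Combining two models (illustration).** Assume one team achieves 4 points and the other 0. With an even split the combined difference is (4 + 0)/2 = 2.
- Power with 35 per phase and SD 6 is 28.0%.
- If the intervention group's variance is allowed to rise because its mean is a mixture, the average variance is (36 + 40)/2 = 38, SD 6.16, and power is 26.8%.

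**4. Precision**, half-width of the 95% CI = t × 6 × √(2/n):

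| Comparison | n per phase | Half-width | Power for 4 points |
|---|---|---|---|
| Combined | 35 | 2.86 | 78.5% |
| One disease | 18 | 4.06 | 49.3% |
| One disease | 17 | 4.19 | 47.0% |

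**5. Difference between the two groups' effects.** Standard error = 6 × √(4/17.5) = 2.87. For effects that differ by 4, power is about Φ(4/2.87 − 1.96) = 29%. Reaching 80% needs 4 × 36 × (1.96 + 0.84)²/16, about 71 per cell. Even then, a detected difference would belong to the disease-and-team combination.

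**6. What stratifying does and does not do.** With equal weights the overall estimate is ½(d_CHF + d_COPD). Its standard error with 17.5 per cell is ½ × √2 × 6 × √(2/17.5) = 1.43, the same as 6 × √(2/35) = 1.43 without strata. In step 3 the estimate is still 2, so power is not restored.

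The gain is protection against a shift in mix. If mean POS differs between the diseases by D and the CHF share of completers differs between phases by Δp, the unstratified difference moves by D × Δp even when the intervention does nothing. The documents give neither quantity. Assuming 20:15 CHF to COPD completers in one phase and 15:20 in the other, Δp = 5/35 = 0.143. The shift is then 0.29 points for D = 2, 0.57 for D = 4 and 0.86 for D = 6. Within strata this shift does not arise.

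**The case against.** The strongest reply has four parts, and much of it stands.

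- **Combined analysis is not stated.** A reader might infer from the 50-against-50 sizing that the before-after analysis, and the adherence and acceptability figures, will be reported only in combined form. The documents do not say so. Data analysis leaves the pairs open and its one example is disease-specific. Table 3 has open columns for findings and evidence. What stands of the concern is narrower: the only before-after contrast with a stated power is the combined one.
- **No bias in the main contrast.** A reader might also infer that the aliasing distorts the treatment effect. It does not, because each disease has its own baseline phase with the same quota of 25. The aliasing limits attribution only.
- **Not everything is aliased.** It would be too strong to treat disease, ward, recruiter and deliverer as one variable. Cardiology has two wards, only screening differs while one researcher approaches everyone, and tool, trainer and flyer step are shared. Delivery team and screening route do coincide with disease.
- **The 28% comes from an assumed extreme.** Nothing in the documents points to 4 against 0, and any cause that halves the average effect gives the same power. The figure illustrates dilution and predicts nothing.

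It can also be said that reporting by ward is detail for an analysis plan. The aliasing itself, however, is set in the published design, and the published rationale and limitations leave it out.

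**Conclusion.** The point holds in a limited form. Delivery team is fully aliased with disease, the powered before-after comparison combines the two, and the article does not acknowledge it. A CHF-COPD difference in effect or feasibility would be a difference between disease-and-team combinations.

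It would go too far to conclude that the study will hide a delivery model that works, or that reporting by group would rescue one. If one team achieved the full 4 points, its own comparison would have only about 47% to 49% power. These figures rest on SD 6, 30% attrition, a two-sided 5% level and an even split of completers; the dilution figure rests also on the assumed 4-against-0 effects. For a single-hospital feasibility study staffed from its own wards, this is a modest but nearly free improvement.

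**What to change.** - Estimate the overall before-after difference stratified by disease, as a combination of the CHF and COPD differences, using the 25/25 quota already set. Unequal mix after recruitment and attrition then does not distort it.
- Report the before-after difference with its 95% CI, and the Table 3 items on recruitment, adherence, acceptability and retention, for each disease-and-team group. Label these results descriptive.
- State in Limitations that team and disease are aliased, and that CHF-COPD differences will be described as differences between disease-and-team combinations.

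The cost is analysis and reporting wording, with no new data. The downside is that per-group estimates are imprecise and invite over-reading, hence the descriptive label. The change neither restores power nor separates team from disease; no sample size can do that while each disease has one team.
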